### 2.11. Termination and withdrawal

Participants may withdraw from the trial for any reason at any time. Withdrawal or dropped visits will also be recorded on CRFs. Investigators will review the CRFs while considering inclusion, exclusion, and withdrawal criteria. Reasons for withdrawal or termination and the last medication time will be detailed in CRFs. All withdrawn and terminated cases will be reported and analyzed.

### 2.12. Sample size estimation

Interpretation of findings by clinical experts. Minimum sample size will be based on a total of 160 subjects (106 vs. 53) that will be assigned to experimental and control groups in a ratio of 2:1 (based on subject number per group). In order to detect any differences between groups with a power of at least 80%, the type I error rate will be calculated based on a 2-sided error detection cutoff of 0.05. If enough subjects can be recruited, the target sample size will be adjusted to include 180 subjects to compensate for loss of subjects as based on a predicted dropout rate of 20%. The 180 subjects will be allocated to groups based on the above mentioned 2:1 ratio (120 subjects in the CHM group, 60 subjects in the placebo group).

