## Abstract

**Methods and analysis::**

A randomized, double-blind, parallel, placebo-controlled multicenter trial will be conducted over the course of 2 weeks. A total of 180 CVA patients of ages between 4 and 7 years old will be randomly assigned to the experimental group (XHJJ granules, 4.5 g administered 3 times daily) or control group (matched placebo, 4.5 g administered 3 times daily) in a 2:1 ratio based on subject number per group, respectively. The trial will consist of a 7-day medical interventional stage and a 7-day follow-up stage. On day 7 of the follow-up stage, an evaluation of all subjects will be carried out to assess cough symptom score as the primary outcome and several secondary outcomes, including TCM (traditional Chinese medicine) syndrome score, lung function, and dosage of salbutamol aerosol inhaler therapy. Safety assessments will also be evaluated during the trial.

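### The Abstract fixes 180 children to be randomised, but section 2.12 makes 180, its only dropout allowance, conditional on recruitment, so the wording permits closing at 160 with no reserve

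*Protocol article*

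**What the plan says.** The Abstract (Methods and analysis) gives the size without condition: "A total of 180 CVA patients of ages between 4 and 7 years old will be randomly assigned".

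Section 2.12 starts from a smaller figure: "Minimum sample size will be based on a total of 160 subjects (106 vs. 53"). It ties that figure to detecting a difference "with a power of at least 80"%, at a two-sided 0.05 level. It then adds: "If enough subjects can be recruited, the target sample size will be adjusted to include 180 subjects". The stated purpose of the increase is "to compensate for loss of subjects as based on a predicted dropout rate of 20"%. The section ends by treating the larger number as settled ("120 subjects in the CHM group, 60 subjects in the placebo group").

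The size is thus stated three times: without condition in the Abstract, conditionally in the middle of section 2.12, and without condition again at its end. The article has no rule for when enrolment stops between 160 and 180, and it gives no effect size or standard deviation behind the 160.

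**The concern.** An allowance for dropout should follow from the loss expected. Here it follows from how recruitment goes. By the section's own account 160 is the number before dropout, and everything added for a loss that the plan itself predicts is optional. A sponsor that stopped at 160, or anywhere up to 180, could say that it had kept to section 2.12, while a reader of the Abstract would say that it had not.

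Two things are at stake. First, if enrolment stopped at 160 and the predicted loss occurred, the analysed number would be below the plan's own minimum, and a null result would be harder to interpret. Second, the results are to be reported under CONSORT (section 2.2), and a report that ended short of 180 could not agree with both statements of planned size.

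**Working it through.** **Inputs from the documents.** Abstract: 180, unconditional. Section 2.12: minimum 160, with arms 106 and 53; target 180 (120 and 60) if recruitment allows; predicted dropout 20%; power at least 80%; two-sided 0.05; allocation 2:1. The arms 106 + 53 sum to 159, a rounding matter of no consequence.

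**Step 1. Can 180 be reproduced from 160 and 20%?**
- 160 / (1 − 0.20) = 200
- 160 × (1 + 0.20) = 192
- From 159 the same two formulas give 199 and 191.

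None of these is 180. Read the other way, 1 − 160/180 = 0.111, so going from 160 to 180 covers about 11% loss.

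**Step 2. Children left after the predicted loss.**
- 160 × 0.80 = 128
- 180 × 0.80 = 144

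Both are below the stated minimum of 160.

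**Step 3. Power.** The 160 cannot be checked, because no effect size or SD is given. Assumption: 106 vs 53 gives exactly 80% power, with an unadjusted two-group comparison and every dropout lost from the analysis. The implied standardised difference is

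d = (1.960 + 0.842) × √(1/53 + 1/106) = 2.802 × 0.1682 = 0.471.

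With N analysed at 2:1, power = Φ(d × √(2N/9) − 1.960).
- N = 128: 0.471 × 5.333 − 1.960 = 0.554, power 71%
- N = 144: 0.471 × 5.657 − 1.960 = 0.706, power 76%

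A noncentral-t version (d = 0.474) agrees within 0.2 percentage points.

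The same calculation for other losses follows. The 0, 5 and 10% columns are illustrative; only 20% is the plan's figure.

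| Randomised | 0% lost | 5% | 10% | 20% |
|---|---|---|---|---|
| 160 | 80% | 78% | 76% | 71% |
| 180 | 85% | 83% | 81% | 76% |
| 200 | 88% | 86% | 85% | 80% |

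**Step 4. Sensitivity to the unstated design power.** The plan says at least 80%, so 106 vs 53 may have been sized for more.

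| Power at 106 vs 53 | Implied d | 160 randomised, 20% lost | 180 randomised, 20% lost |
|---|---|---|---|
| 80% | 0.471 | 71% | 76% |
| 85% | 0.504 | 77% | 81% |
| 90% | 0.545 | 83% | 87% |

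For 128 analysed children still to give 80%, the power at 160 would have to be about 88%.

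**Step 5. What the clause alone costs.** The difference between the two last columns of Step 4 is about 4 to 5 percentage points of power. At equal proportional loss, the standard error is larger by √(180/160) = 1.06, or about 6%.

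**The case against.** **The clause may be only a feasibility caveat.** Two of the three statements of size fix 180, and section 2.12 itself calls 180 the target. No sentence says that enrolment may end at 160, and a recruitment-closing rule is often left to the full protocol. A reader might infer that the sponsor plans to stop at 160; the article does not say so. What stands is narrower: the article does state a condition, that condition conflicts with the Abstract, and its wording leaves a close at 160 open.

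**The power figures are back-solved.** A reader might infer that 80% power holds at 160 only if no child is lost. The documents do not support that. The plan says at least 80% and gives no effect size, so there may be slack; a design power of 90% would leave about 83% after 20% loss. Even with exactly 80%, one or two withdrawals hardly matter. This part of the objection stands, and the figures should be read as a range.

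**Dropouts may not be lost, and the planned analysis is not a t test.** Section 2.14 makes intention-to-treat the main analysis, and section 2.11 says withdrawn cases will be reported and analysed. The primary outcome averages daily diary scores (sections 2.2 and 2.9), so a child who stops early may still contribute. Section 2.14 also plans ANCOVA with baseline score and site when its assumption is met. If 160 came from an unadjusted comparison, which is not stated, a baseline correlation of about 0.45 (an assumption: 1 − 0.45² ≈ 0.80) would offset a 20% loss. These points could soften the shortfall. They do not show that it is absent, because the intention-to-treat definition is still to be finalised and the basis of the 160 is not given.

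**An open end to enrolment need not bias the result.** A reader might infer that the size could be settled with an eye on outcomes. Sections 2.2 and 2.8 blind investigators, assessors and statisticians, and no interim comparison is described. Closing on recruitment grounds under blinding costs precision, not validity.

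**Fixing 180 does not deliver 80% at the predicted loss.** This is correct: 144 remain, with about 76% power under the base assumption. It is a reason to widen the correction. It does not excuse the clause, since a better-inflated target with the same condition attached would still allow a close at 160.

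**Conclusion.** The concern holds as an inconsistency in the stated sample size that bears on the stated power. The Abstract fixes 180; section 2.12 makes 180, and with it the whole dropout allowance, depend on recruitment.

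If the trial closed at 160 and lost 20%, 128 children would be analysed. Power would then be about 71% if 106 vs 53 gives exactly 80%, about 77% if it gives 85%, and about 83% if it gives 90%. With 180 randomised the corresponding figures are about 76%, 81% and 87%. All of these rest on a two-sided 0.05 unadjusted t test and on dropouts leaving the analysis; baseline adjustment or partial diary data could recover some of the loss. The contradiction itself rests on no assumption.

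The documents do not establish that the trial will close at 160, that the stated power fails with the first withdrawal, or that the result would be biased. The point is worth correcting because it affects a headline design figure and the correction is cheap.

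**What to change.** In section 2.12, delete the conditional clause and state one fixed number to randomise that agrees with the Abstract (180, as 120:60).

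In the same edit, reconcile 160, 180 and 20%. As 180 covers only about 11% loss and leaves 144 at 20%, restate either the dropout rate that 180 covers or the power expected with 144 analysed. That power should be computed from the sponsor's own effect size and SD, not from the back-solved values used here.

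If an earlier close is to remain possible, name it as a contingency decided on recruitment alone, without sight of outcome data. State the power at 160 randomised with the predicted loss, and align the Abstract.

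The cost is a few sentences. No child is added beyond the 180 that the Abstract already commits to. The downside is a possibly longer recruitment period, or a less favourable power figure in print.

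### The 180-child target does not absorb the predicted 20% dropout from the plan's own minimum of 160, so the stated power is not supported under that forecast

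*Protocol article*

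**What the plan says.** Everything needed is in section 2.12 (Sample size estimation) of the protocol article, with one cross-reference to the abstract.

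- Minimum: "Minimum sample size will be based on a total of 160 subjects (106 vs. 53"), with children "assigned to experimental and control groups in a ratio of 2:1".
- Operating characteristics: differences are to be detected "with a power of at least 80" per cent, with type I error "based on a 2-sided error detection cutoff of 0.05".
- Dropout and target: the total is to be "adjusted to include 180 subjects to compensate for loss of subjects as based on a predicted dropout rate of 20" per cent, but under a condition: "If enough subjects can be recruited, the target sample size will be adjusted to include 180 subjects". The section then splits the 180 as 120 and 60.
- The abstract gives the same total without any condition: "A total of 180 CVA patients of ages between 4 and 7 years old will be randomly assigned".

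The section states no effect size, no standard deviation and no test on which the 160 was based.

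**The concern.** The section gives a required number, a predicted loss and a recruitment target, and says that the target was set to cover the loss. A reader can check that link directly, and it fails: the target is too small for the loss it is said to cover.

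The power statement is what is at stake. It is attached to the 160 minimum. If the trial loses as many children as it predicts, it will analyse fewer than that minimum, and a non-significant result would be read against a power that the article has not shown the design to have. In addition, section 2.12 makes the step from 160 to 180 depend on recruitment. Taken literally, the whole dropout allowance is optional, which does not agree with the abstract.

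**Working it through.** **Inputs, all from section 2.12:** minimum N = 160 (arms 106 and 53); allocation 2:1; predicted dropout d = 0.20; target 180 (120 and 60); power at least 80%; two-sided alpha 0.05.

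**1. Can the 180 be reproduced?**

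| Rule | From 160 | From 106 + 53 = 159 |
|---|---|---|
| N/(1 − d) | 160/0.8 = 200 | 159/0.8 = 198.75, so 199 |
| N × (1 + d), a common mistake | 192 | 190.8, so 191 |

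An exact 2:1 split at or above 200 is 134 + 67 = 201. None of these gives 180, and the gap is too large for rounding.

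**2. What does 180 leave after 20% loss?** 180 × 0.8 = 144; by arm, 120 × 0.8 = 96 and 60 × 0.8 = 48. That is 16 below 160 and 15 below 159.

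**3. What loss does 180 cover?** 1 − 160/180 = 11.1%; from 159, 1 − 159/180 = 11.7%. Either is little more than half of the predicted 20%.

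**4. What might this do to power?** This step needs an assumption, because the article gives neither an effect size nor an SD. Suppose that 106 vs 53 gives exactly 80% power in an unadjusted two-group comparison of means.

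- Standard error in SD units at 106 vs 53: √(1/106 + 1/53) = 0.1682.
- Implied standardised effect: (1.960 + 0.842) × 0.1682 = 0.471 (normal approximation; 0.474 with the t distribution).
- Standard error at 96 vs 48: √(1/96 + 1/48) = 0.1768.
- Power at 96 vs 48: Φ(0.471/0.1768 − 1.960) = Φ(0.706) = 76.0% (75.9% with the t distribution).

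The same steps with other planned powers at 106 vs 53 give:

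| Power assumed at 106 vs 53 | Power at 96 vs 48 | Power at 120 vs 60 (no dropout) |
|---|---|---|
| 80% | about 76% | about 85% |
| 85% | about 81% | about 89% |
| 90% | about 87% | about 93% |

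The break-even is near 84%: if 106 vs 53 was planned at that power or higher, 96 vs 48 still reaches 80%.

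**5. Arm sizes.** 106 + 53 = 159, not 160. Because 160 does not divide 2:1 (106.67 and 53.33), this is a rounding slip with no consequence of its own.

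**The case against.** A reader might infer that the trial is shown to have less than 80% power, with 76% as the true figure and about 0.47 SD as its design effect. The document does not support that. The article promises at least 80%, not exactly 80%, and gives no effect size or SD. The 0.47 SD is back-solved from an assumption, and with a planned power near 84% or more the 144 would still suffice. This part of the objection stands, so the power figures can only be given as a range.

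A second line of defence is that 144 may not be the number in the primary analysis. Section 2.14 makes intention-to-treat the main analysis, section 2.11 says withdrawn cases will be analysed, and the outcome in section 2.9 averages scores over days, so a child who leaves early may still contribute. Section 2.14 also plans ANCOVA with the baseline score, which may recover precision. These points add uncertainty to the size of any power loss. They do not rescue the arithmetic: section 2.12 itself treats dropouts as losses to be made up, and claims no gain from retained data or from covariates.

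Third, a reader might infer from the conditional wording that the trial could stop at 160 randomised and still claim 80% power. That goes too far. The section ends by allocating all 180 children and the abstract fixes 180. The phrase is loose and needs reconciling, but it is no evidence of such an intention.

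Finally, the shortfall arises only if losses approach the forecast. With full retention, 180 exceeds the minimum. Neither bias nor type I error is affected.

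**Conclusion.** The inconsistency holds on the document's own figures and needs no outside input. A target of 180 does not compensate for 20% dropout from 160: it leaves 144 (96 vs 48), where 200 randomised would be needed (201 at exact 2:1), and it covers a loss of only about 11%. This is true whatever power was planned.

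It follows that the stated power is not supported under the plan's own dropout forecast. That is weaker than saying power falls below 80%. On the assumption of exactly 80% at 106 vs 53 (two-sample comparison, two-sided 0.05), the figure at 96 vs 48 is about 76%, a loss of about 4 percentage points. At a planned 85% or 90% it is about 81% or 87%. Only the sponsor's own effect size and SD can settle which applies.

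The conditional wording on the 180 is a lesser inconsistency with the abstract, and the 159 against 160 is a tidy-up.

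**What to change.** Change section 2.12 only, in one of two ways:

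- **(a)** State that 180 randomised (120:60) preserves the minimum of 160 only for dropout up to about 11%, and say why a loss of that size is expected in place of 20%; or
- **(b)** Keep the 20% forecast, state that it leaves 144 evaluable (96:48), and restate the power at that size from the sponsor's own effect size and SD. The back-solved 0.47 SD should not be printed as the design effect.

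In either case, drop the recruitment condition so that 180 is the fixed target, as in the abstract. Also make the arm sizes agree with the total: either 159 (106 + 53) or 160 (107 + 53).

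The cost is a few sentences and possibly a less favourable stated figure. No additional children are enrolled, and the design and analysis do not change.

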### 2.13. Data management and quality control

All investigators on the study team will be trained to follow standard operating procedures and strictly adhere to the protocol during the entire study period. Investigators will be reminded to finish CRFs completely and correctly in a timely manner according to information obtained from original medical records. Lung function and blood tests will be conducted by qualified medical professionals.

Investigators from the Affiliated Hospital of Changchun University of TCM will visit each site once a month to audit the quality of data collection and resolve any issues encountered at the sites. All documents will be properly secured and preserved under confidential conditions and archived.

### 2.14. Statistical analyses

Statistical analysis will be conducted by an independent statistician from the Beijing University of Chinese Medicine. The statistician will follow a detailed statistical analysis plan that was drafted separately by a different statistician before trial inception. Results of statistical analysis will be finalized before trial unblinding. Baseline characteristics will be described using mean ± SD for continuous data and number and percentage for categorical and hierarchical data. Inferential analysis of continuous data will rely on use of *t* tests or the Wilcoxon rank sum test depending on whether the assumption of normal distribution is met or not. Chi-squared or Fisher’s exact tests will be used to compare categorical data between groups. ANCOVA will be applied when the assumption is met for analysis of the primary outcome, with the covariates including baseline score and study site. In addition, the interaction between study site and group will be considered in this model.

The main analyses to determine drug effectiveness will follow intention to-treat (ITT) analytical principles, with the definition of ITT agreed upon and finalized before trial unblinding. Analysis of the per-protocol set of data will be conducted and the results will be used to complement results of ITT analysis. The safety analysis set of data will be the main data set used for safety analyses.

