#### 2.2..2. Study design and procedure.

This trial will consists of a 7-day medical intervention stage and a 7-day follow-up stage (Figure 1)and will be carried out concurrently in 6 hospitals in China: the Affiliated Hospital of Changchun University of traditional Chinese medicine (TCM), Changchun; the Affiliated Hospital of Beijing University of TCM, Beijing; the Affiliated Hospital of Liaoning University of TCM, Shenyang; the Affiliated Hospital of Shandong University of TCM, Shandong; the Jiangsu Hospital of TCM, Nanjing; and the First Affiliated Hospital of Henan University of TCM, Henan.

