**Figure 1. F1:**
[figure not shown]
Flowchart of this study.

Patients will be invited to participate in an initial assessment (first visit), during which they will be selected or rejected for enrollment according to results of screening based on inclusion and exclusion criteria. Next, eligible patients will receive physical examinations to assess TCM syndrome scores, as well as laboratory testing that will include whole blood counts, routine blood and urine testing, liver and kidney function testing, electrocardiography, and chest radiography. Participants will be randomly assigned to the experimental group (receiving XHJJ granule) or the placebo group and will be blinded with regard to group assignments. Patient self-reported cough symptom scores and TCM syndrome scores will be recorded daily in patient diaries during the treatment period.

Patient face-to-face interviews with blinded assessors will be scheduled on the fourth day (second visit) in order to collect relevant clinical data, including lung function assessments and blood tests, as well as data pertaining to quality of life, safety, and drug usage. Beginning on the seventh day (third visit) and throughout the second week (the follow-up stage), participants will continue to self-report cough symptom scores and TCM syndrome scores daily in their diaries and document their utilization of health resources (including any drug use). During the last visit on day 7, quality of life, lung function, adverse events (AEs), and drug usage will be assessed and participants will undergo blood tests. An overview of specific measurements and time points for data collection is presented in (Table 1).

**Table 1 T1:** Measurement items and point of data capture.

Study period	Screening period (d)	Medication (d)		Safety follow-up
	Visit 1 (−7 to 0)	Visit 2 (4 d)	Visit 3 (7 d)	
Sign informed consent	√			
Fill in general information	√			
Medical history and treatment history	√			
Physical examination	√		√	
chest radiographs	√			
Lung function	√		√	
TCM syndrome score	√	√	√	
Vital signs	√	√	√	√
Routine blood test	√		√	√
Routine urine test	√		√	√
ECG, liver, and kidney function	√		√	√
Adverse event		√	√	√
Distribution of experimental drugs	√	√		
Test drug recovery		√	√	
Issue diary card	√			
Recycle patient’ s diary card			√	
Comorbidity and medication records	√	√	√	
Compliance evaluation		√	√	
Safety assessment		√	√	

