#### 2.9..2. Secondary outcomes.

TCM syndrome score;Lung function;Dosage of salbutamol aerosol.

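### The only stated test for continuous secondary outcomes is unadjusted, although lung function and the TCM syndrome score have baseline values that could sharpen the comparison

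*Protocol article*

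**What the plan says.** Section 2.14 (Statistical analyses) of the protocol article states for continuous outcomes: "Inferential analysis of continuous data will rely on use of *t* tests or the Wilcoxon rank sum test", with the choice between the two resting on normality. For the primary outcome it adds: "ANCOVA will be applied when the assumption is met for analysis of the primary outcome, with the covariates including baseline score and study site". It also says that the interaction of site and group will be considered in that model. No adjusted analysis is stated for any other outcome.

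Section 2.9 lists the secondary outcomes as "TCM syndrome score;Lung function;Dosage of salbutamol aerosol". Table 1 ("Measurement items and point of data capture") ticks the TCM syndrome score at Visits 1, 2 and 3. It ticks lung function at screening and once on treatment, by layout Visit 3. The text on study procedure also puts the TCM score at the initial assessment: "eligible patients will receive physical examinations to assess TCM syndrome scores". Both outcomes therefore have a value before treatment. Section 2.2 says that the trial "will be carried out concurrently in 6 hospitals in China", so site would take five terms in a model.

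**The concern.** The plan accepts a child's own baseline and the hospital as covariates for the cough score. It gives no reason for leaving them out for two other outcomes with a baseline measurement. Followed as written, the between-group tests of lung function and the TCM syndrome score do not use study site, and use the Visit 1 value at most through a simple change score. If baseline predicts the later value, confidence intervals for these outcomes will be wider than the collected data allow. The placebo arm has only 60 children and section 2.12 states no power for any secondary outcome, so their precision is not protected elsewhere.

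**Working it through.** **The plan's own figure.** Section 2.12 gives 106 vs 53 for at least 80% power at two-sided 0.05, with no effect size or SD, so it cannot be reproduced. Solved backwards by the normal approximation, it implies a standardised difference of (1.960 + 0.842) × √(1/106 + 1/53) = 0.471. The article gives no power or precision figure for secondary outcomes.

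**Inputs.** Allocation 120 vs 60 and two-sided 0.05 are from section 2.12, and six sites from section 2.2. The correlation ρ between Visit 1 and the later value is not in the article and is varied. The reference effect is the one that an unadjusted t test detects with 80% power at 120 vs 60: d = 0.445 (noncentral t, 178 df). Site is assumed to explain no variance, which works against adjustment.

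**Formulas.**
- ANCOVA variance relative to a t test on day-7 values: 1 − ρ².
- A t test on change has variance 2(1 − ρ), so the ANCOVA variance relative to it is (1 − ρ²) / [2(1 − ρ)] = (1 + ρ)/2.
- Estimating p covariate terms inflates the variance by f = 1 + p/(N − p − 3). With p = 6 (baseline plus five site terms) and N = 180, f = 1 + 6/171 = 1.035, with 172 df.
- Noncentrality = 0.4454 / √[ratio × f × (1/120 + 1/60)]. With ratio and f both 1, this is 0.4454/0.1581 = 2.817, the 80% reference.

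**Compared with a t test on day-7 values (80% power).**

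| ρ | 1 − ρ² | × f | Noncentrality | ANCOVA power |
|---|---|---|---|---|
| 0 | 1.00 | 1.035 | 2.769 | 78.6% |
| 0.3 | 0.91 | 0.942 | 2.902 | 82.3% |
| 0.5 | 0.75 | 0.776 | 3.197 | 88.9% |
| 0.7 | 0.51 | 0.528 | 3.877 | 97.1% |

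**Compared with a t test on change.** Here the effect is rescaled so that the change-score test has 80% power.

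| ρ | (1 + ρ)/2 | × f | Noncentrality | ANCOVA power |
|---|---|---|---|---|
| 0.5 | 0.75 | 0.776 | 3.197 | 88.9% |
| 0.7 | 0.85 | 0.880 | 3.003 | 84.8% |
| 0.8 | 0.90 | 0.932 | 2.918 | 82.7% |
| 0.9 | 0.95 | 0.983 | 2.841 | 80.6% |

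**Where the gain is small.** Solving for 85% power, the gain is under 5 points if ρ is below about 0.39 (day-7 values) or above about 0.69 (change).

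**Cost.** At ρ = 0 the full model loses 80.0 − 78.6 = 1.4 points. Break-even against day-7 values is at ρ of about 0.19. With baseline alone, f = 1 + 1/176 = 1.006 and the loss at ρ = 0 is about 0.2 points.

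**Smaller samples.** With the effect reset to give the t test 80% power, 106 vs 53 (d = 0.474, f = 1.040) gives 82.1%, 88.7% and 97.0% at ρ of 0.3, 0.5 and 0.7 for day-7 values. After 20% loss, 96 vs 48 (d = 0.499, f = 1.044) gives 81.9%, 88.6% and 97.0%. The picture is unchanged.

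**The case against.** The sentence on t and Wilcoxon tests is generic. It follows the description of baseline characteristics, names no secondary outcome, and does not say whether final values or changes are compared. The ANCOVA sentence does not exclude wider use. Section 2.14 refers to a separate analysis plan that is not shown and that may adjust these outcomes. This stands as a limit: a reader might infer that the trial has decided against adjustment, and the article does not show that. But the generic sentence is the only method stated for continuous outcomes, and ANCOVA is named for one outcome. If the analysis plan does adjust, the article's wording still needs aligning with it.

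The gain also rests on an assumed correlation. Entry requires a daytime plus nighttime cough score of at least 4 (section 2.3) and a particular syndrome pattern (section 2.4). That may narrow the baseline range of the TCM score and lower ρ. This stands, and is why only a range is given.

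Two stronger readings are tempting. One is that chance baseline imbalance makes the unadjusted comparison misleading. Under randomisation the test is unbiased and keeps its type I error, and its standard error already allows for chance imbalance. The other is that lung function must gain most because children aged 4 to 7 differ widely before treatment. The article gives no figure for that spread and does not name the lung-function parameter. A percent-predicted measure would already remove much of the age-related spread. If change were tested, a high correlation would make the gain smaller.

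**Conclusion.** The point holds as a modest loss of precision in two secondary outcomes. The stated tests are valid, and the primary analysis already adjusts for baseline and site. At 120 vs 60 and an assumed ρ of 0.5, adjustment adds about 9 points of power whether the alternative is a t test on day-7 values or on change. The gain runs from about 2 to 17 points over ρ of 0.3 to 0.7 for day-7 values. For change it falls from about 9 points to under 1 as ρ rises from 0.5 to 0.9. These figures assume normal outcomes, a reference effect set at 80% power, and no variance explained by site. A reader might conclude that adjustment is free. That is true of data collection, but the model can cost about 1.4 points if the covariates predict nothing.

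**What to change.** In section 2.14, state that lung function and the TCM syndrome score, at their planned endpoint, are analysed by ANCOVA with treatment group, the outcome's own Visit 1 value and study site. Apply the same condition on assumptions as for the primary outcome, and name a baseline-adjusted rank-based analysis as the fallback. Report the adjusted difference with its 95% confidence interval. Keep the t or Wilcoxon tests for continuous variables with no baseline, such as salbutamol dosage.

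The cost is one sentence here and in the analysis plan before unblinding, with no new data, visits or patients, plus six model degrees of freedom. If the site terms are thought too many for these outcomes, baseline alone keeps most of the benefit.
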